## Abstract

**Background:**

Dementia and cognitive decline are serious social and economic burdens. An increase in the population of older people, as well as longer lifespans mean that numbers of dementia cases are exponentially rising. Neuropathological changes associated with dementia are thought to appear before the clinical manifestation of cognitive symptoms, i.e., memory impairments. Further, some older adults (OA) experience cognitive decline before it can be objectively diagnosed. For optimal care of these patients, it is necessary to detect cognitive decline and dementia at an early stage. In this vein, motor, sensory, and neurophysiological declines could be promising factors if found to be present before the onset of cognitive impairment. Hence, the objective of the SENDA study is to develop a multi-dimensional sensor-based instrument that allows early detection of cognitive decline or dementia in OA with the help of cognitive, sensory, motor, and neurophysiological parameters before its clinical manifestation.

**Methods/design:**

In the cohort sequential study, participants are assigned to one of three study groups depending on their cognitive status: 1. cognitively healthy individuals (CHI), 2. subjectively cognitively impaired persons (SCI), or 3. (possible) mildly cognitively impaired persons (pMCI, MCI). All groups take part in the same cognitive (e.g., executive function tests), motor (e.g., gait analyses, balance tests), sensory (e.g., vibration perception threshold test, proprioception tests), and neurophysiological (e.g., electroencephalograms) measurements. Depending on the time at which participants are included into the study, all measurements are repeated up to four times in intervals of 8 months within 3 years to identify associations with cognitive changes over time.

**Discussion:**

This study aims to detect possible motor, sensory, neurophysiological, and cognitive predictors to develop an early screening tool for dementia and its pre-stages in OA. Thus, affected persons could receive optimal health care at an earlier time point to maintain their health resources.

**Trial status:**

The study is ongoing. The recruitment of participants will be continued until May 2020.

## Background

Dementia is a common age-related neurodegenerative disease whose prevalence is increasing globally. According to the German Alzheimer Society e.V. [1], the number of dementia cases in Germany will have risen to three million by 2050. In addition to the personal cost, the disease causes substantial economic and social burdens [2]. Early diagnosis of dementia and its pre-stages could alleviate these by enabling sustainable disease management and optimal health care for affected individuals.

Although no effective treatment of dementia exists yet, early diagnosis has been shown to enable interventions which slow down disease progression (i.e. physical activity interventions [3] or pharmaceutical interventions [4]). Early diagnosis provides the opportunity to start treatment before neurodegeneration has progressed and with only minimal disease pathology present [5]. The deterioration of cognitive functions, e. g., memory, attention, or executive functions, is a typical symptom of this illness [6]. Additionally, patients with dementia show anomalies in their social behavior and activities of daily living (ADL) [6]. Mild cognitive impairment (MCI) is classified on a continuum between cognitive changes of normal aging and symptoms of dementia [7]. In this vein, people with MCI have a 10-fold increased risk of developing dementia [8]. Patients with MCI are characterized by the following criteria: (1) concerns about changes in cognition by themselves or someone else, (2) impairments in at least one cognitive domain, and (3) no problems in ADL [9]. Cognitive impairments most often pertain to memory, but can also include other cognitive domains, such as executive functions, attentional control, language skills, or visuospatial skills [9]. Interestingly, a substantial amount of older people report memory loss and other cognitive deficits even in the absence of objective cognitive impairments [10]. The condition has been classed as SCI, meaning subjective cognitive impairment, as people subjectively experience worsening of their cognitive performance compared to prior performance levels while they still perform within normal range on standard clinical assessments of cognition [11]. SCI has been shown to triple the risk of Alzheimer’s disease [12], is associated with underlying dementia neuropathology [13], and as such could be considered an even earlier pre-clinical stage of dementia [11].

Brain imaging, e.g., computed tomography or magnetic resonance imaging, laboratory tests, and cognitive or neuropsychological tests are standard methods of diagnosing dementia [6, 14]. However, by the time individuals receive the diagnosis, cognitive impairments will generally have progressed [5, 15]. Neuropathological changes associated with dementia have been found to develop before the clinical manifestation of cognitive symptoms, i.e., memory impairments [5], and might be expressed in SCI or even MCI. Since the costs are too high to use neuroanatomical and biological markers for diagnosis [9], it is worthwhile to explore whether behavioral markers, other than cognitive performance, can be used to successfully predict the development of dementia. If successful, it would provide a low cost and easy to apply approach to screening for dementia at the pre-clinical stage, and enable appropriate interventions to be established to delay its clinical manifestations. Consequently, current research aims to determine prodromal markers for early detection of dementia, for example, changes in the motor (e.g. abnormalities in gait) or the sensory systems [16].

With regard to motor control, persons with MCI present a transitional stage between healthy controls and patients with early Alzheimer’s disease [17]. For example, identifying abnormalities in gait parameters are a key focus in early screening for dementia [18–20]. A meta-analysis of Bahureska et al. [18] revealed that lower gait velocity, termed senile gait [21, 22], seems to be a marker to discriminate between MCI and healthy controls [19]. Additionally, poor performance walking under more complex conditions, such as dual-task conditions, has been associated with higher risk of developing dementia [19, 23, 24].

Furthermore, other motor changes might be used for predicting dementia, e.g., dynamic balance control, finger dexterity, and cutaneous sensitivity*.* Many anatomical structures (e.g., the brainstem, spinal cord, or the primary somatosensory cortex [25–29]), associated with processing cutaneous sensations, are negatively affected in dementia, early dementia, or its precursor MCI. To date, however, there are only few studies which investigate cutaneous sensitivity in MCI patients or dementia diseases [30]. Cutaneous sensitivity is essential for motor performance [31], gait [32], and balance [33]. Quasi-static balance [34] has already been identified as a prodromal marker of dementia [18], whereas dynamic balance with unexpected perturbations has not yet been explored in patients with MCI. Changes in finger dexterity could be predictors for the development of dementia [35], independently from age-related changes [36]. For instance, Rabinowitz and Larner [37] revealed that patients with MCI or dementia show an increase in duration and variability of the finger-touch phase during finger tapping compared to cognitively healthy OA.

Furthermore, neurophysiological techniques, including electroencephalography (EEG), enable detection of functional changes in brain activity at an early stage of dementia [38, 39]. Resting state EEG reveals differences between persons with dementia or pre-clinical dementia and healthy OA [38, 39]. The limited number of longitudinal studies have identified the mean frequency of the total spectrum [40], relative beta power [41], relative alpha power [41–44], relative theta power [40, 42, 45], coherence across all frequencies [40], and coherence in the delta band [46] as possible predictors of cognitive decline. Unfortunately, there is not yet a clear consensus about which parameters best predict dementia or how to translate these findings into cut-offs for individual diagnosis.

In conclusion, early detection of dementia at the presymptomatic stage of disease using prodromal markers is important to detect progressive changes of the central nervous system and to initiate targeted and optimal health care as early as possible. There are, however, only few studies which investigate different markers (e.g., biomarkers, cognitive markers) to detect cognitive decline or the transition from MCI to dementia [47–51]. Gomar et al. [47] examined different biomarkers (e.g., total tau, Aβ1–42), cognitive markers (working memory), and risk factors (APOE genotype) in one study to predict transition from MCI to Alzheimer’s disease. They were able to show that cognitive markers predict these transitions more than most biomarkers. This was also shown in a 4 year follow-up data phase [48]. Another longitudinal study (The Sydney Memory and Ageing Study) by Lipnicki et al. [52] revealed that older age, slower walking speed, and APOE ε4 carrier at baseline were associated with MCI or dementia after 6 years. In a current gait and balance platform study (part of the Ontario Neurodegenerative Research Initiative (ONDRI) by Montero-Odasso et al. [53]), motor-cognitive profiles across neurodegenerative diseases, e. g. Alzheimer’s diseases or MCI, will be identified over 3 years using gait and balance tests. However, to our knowledge, other than the ONDRI study [54], there are no other studies investigating cognitive, motor, sensory, and neurophysiological markers in combination to develop a multi-dimensional instrument to predict cognitive decline or dementia. Therefore, the objective of the current study is to develop such a multi-dimensional sensor-based instrument to detect cognitive decline or dementia in older adults with the help of several cognitive, sensory, motor, and electroencephalogical parameters in a longitudinal cohort. The results of this study will lead to a better understanding of the different prodromal markers and their interaction, and might help to predict MCI or dementia.

This study is named “Sensor-based systems for early detection of dementia (SENDA)” and is funded by the European Social Fund and the Sächsische AufbauBank-Förderbank (SAB) of the Free State of Saxony (Project-Number: 100310502).

## Methods

### Study aims

The following main research question investigated in this study is:

Which cognitive, sensory, motor, and neurophysiological variables are predictors of the transition from subjective cognitive impairment or MCI to dementia in comparison to age-matched healthy OA?

The objective of the SENDA study is to develop a multi-dimensional sensor-based instrument based on the stated variables or their combination to detect cognitive decline or dementia in OA.

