#### Study design

The SENDA study is designed as a prospective cohort sequential study. After successful screening for study eligibility, participants are assigned to one of three study groups depending on their cognitive status based on their MoCA (Montreal Cognitive Assessment), CERAD-Plus (Consortium to Establish a Registry for Alzheimer’s Disease), and the FLei (‘Fragebogen zur geistigen Leistungsfähigkeit’, questionnaire for complaints of subjective cognitive disturbances) scores: 1. cognitively healthy individuals (CHI), 2. subjectively cognitively impaired persons (SCI), 3. possible mildly cognitively impaired persons due to inconclusive test results (pMCI), or mildly cognitively impaired persons (MCI). During the study period participants of four cohorts will be recruited at different time points (see Table 2). All participants complete the same cognitive, motor, sensory, and neurophysiological tests. Depending on the time point of study entry, all tests are repeated up to four times (time points: T1, T2, T3, T4) in intervals of 8 months within 3 years to identify associations with cognitive changes over time (see Fig. 1 for the study design and Table 2). The interval of 8 months was chosen according to Chamberlain et al. [55]. Only this frequency of follow-ups enables the measurements to be repeated up to three times in the defined funding period of 3 years. One test consists of three examination days of 1 to 2 h each.

**Table 2 Tab2:** Time points of study recruitment of the four cohorts and number of follow-up surveys (T1: Baseline; T2-T4: Follow-up surveys; ‘X’: participation; ‘-’: no participation)

Cohorts	T1	T2	T3	T4
Cohort 1 (begin: February 2018)	X	X	X	X
Cohort 2 (begin: July 2018)	X	X	X	-
Cohort 3 (begin: January 2019)	X	X	-	-
Cohort 4 (begin: January 2020)	X	-	-	-

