#### Cognitive status

All prior introduced neuropsychological assessments are used to establish the cognitive status of each participant at baseline and each follow-up. All criteria including cut-offs can be found in Table 3. Cognitive decline is defined as a change from CHI to SCI, pMCI, or MCI, as well as a change from SCI to pMCI or MCI or from pMCI and MCI to dementia. Individuals are categorized as having dementia when they receive a clinical dementia diagnosis outside of the study at any follow-up. Furthermore, participants are categorized as having dementia if they score less than 19 points in the MoCA [62] and perform worse than 1.5 SD below the norm in multiple cognitive domains of the CERAD-Plus. If so participants are advised to visit their general practitioner for further evaluation regarding dementia and to give a feedback to the study coordinator of SENDA as soon as possible. Additionally, functional limitations in ADL and the presence of depression will also be taken into account (see section ‘Questionnaire battery’).

**Table 3 Tab3:** Criteria for cognitive status of the participants

Group	Cognitive Status	Measures		
		MoCA	CERAD-Plus	Flei
Group 1	CHI	30–26	All tests within normal range (≤ 1.5 SD)	≤ 30
Group 2	SCI	30–26	All tests within normal range (≤ 1.5 SD)	> 30
Group 3	pMCI	30–26	1 or more tests below normal range (≥ 1.5 SD)	not considered
		< 26	All tests within normal range (≤ 1.5 SD)	not considered
	MCI	< 26	1 or more tests below normal range (≥ 1.5 SD)	not considered

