### Statistical analyses

A multiple regression model (with e. g. ordinary least squares technique) is used to detect several predictors or mediators of cognitive decline. To identify the most parsimonious model, and with it the final predictors, we analyze the corresponding coefficients of determination and consider the multiple comparisons problem providing a proper method to counteract it. Additionally, we propose an alternative classification taking hand of the k-nearest neighbors algorithm. Furthermore, we analyze changes in motor, sensory, electroencephalogical, and cognitive parameters over time in all three groups using mixed-effects models to explain the correlations in repeated measures in the same subject. Hazard ratios of progressing to dementia for participants with cognitive, motor, sensory, and neurophysiological decline are obtained in the classical way using the Cox semi-parametric proportional hazard model. Several variables are included as potential confounders, such as sex, age, education, comorbidities, psychological status, and social support. The most appropriate procedure for handling missing data will be selected after inspecting the amount and pattern of missing data.

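### The main question uses healthy older adults as comparator for the SCI/MCI-to-dementia transition, and the dementia Cox model as described only partly removes the resulting confounding by baseline status

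*Protocol article*

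**What the plan says.** All references are to the protocol article.

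- **Study aims.** The main question asks which variables predict the "transition from subjective cognitive impairment or MCI to dementia in comparison to age-matched healthy OA". No section names SCI or MCI participants who stay stable as the comparator.
- **Study design.** At entry, "participants are assigned to one of three study groups depending on their cognitive status": CHI, SCI, or pMCI/MCI. Group sizes are not given.
- **Cognitive status.** "Cognitive decline is defined as a change from CHI to SCI, pMCI, or MCI, as well as a change from SCI to pMCI or MCI"; the definition then adds the step from pMCI and MCI to dementia. Decline is thus a change from the participant's own earlier status.
- **Statistical analyses.** A multiple regression "is used to detect several predictors or mediators of cognitive decline". Mixed models describe change "over time in all three groups using mixed-effects models". A Cox model gives "Hazard ratios of progressing to dementia for participants with cognitive, motor, sensory, and neurophysiological decline". The named confounders are "such as sex, age, education, comorbidities, psychological status, and social support". Cognitive status at T1 is not named, and no restriction of the risk set or stratification is stated.

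**The concern.** A predictor of a transition has to separate people who make it from people in the same starting state who do not. Healthy older adults cannot move from SCI or MCI to dementia. Comparing progressors with them mixes being impaired already with being about to progress. Better age matching would not help.

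The article shows that the problem is not hypothetical. Its Background reports that gait velocity already discriminates MCI from healthy controls, and that finger tapping differs in MCI or dementia. Both are candidate markers here.

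Baseline status is also tied to the outcome. The test-based route to dementia needs a MoCA score below 19, together with CERAD-Plus deficits in several domains, and people below 19 are excluded at entry. A participant entering with MoCA 19-25 needs a fall of 1 (19 to 18) to 7 points (25 to 18). A CHI participant at 26-30 needs a fall of 8 to 12 points. T1 status is therefore linked to both marker and outcome, which makes it a confounder.

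At stake is the selection of markers for an early-detection tool. The Abstract's rationale is signs that "could be promising factors if found to be present before the onset of cognitive impairment". A marker chosen by contrast with healthy people may only re-detect what MoCA and CERAD-Plus already show.

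**Working it through.** The article gives no conversion rate, group share or marker effect size for this question, so there is no stated figure to reproduce. The check asks how often a marker that carries no information on progression within any group would be called a predictor.

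**Inputs from the article.** 200 participants for analysis and α = .05 (Sample size; taken here as two-sided). Follow-up of at most 3 × 8 = 24 months from T1 to T4 (Study design).

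**Assumed inputs.** One third healthy (67) and 133 impaired; 10% or 20% of the impaired and 1% of the healthy reach dementia. The marker is shifted by d standard deviations in impaired against healthy people and is unrelated to progression within groups.

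**Step 1: discrimination against healthy people.** AUC = Φ(d/√2).
- d = 0.5: Φ(0.354) = .64
- d = 0.8: Φ(0.566) = .71

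The AUC against stable people of the same status is .50.

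**Step 2: rejection rate of the literal contrast in the main question.** Approximate power = Φ(d·√(n₁n₂/(n₁+n₂)) − 1.96), with n₁ = 67 healthy and n₂ = 133 × 0.10 ≈ 13 or 133 × 0.20 ≈ 27 progressors.
- d = 0.5, 13 progressors: Φ(0.5 × 3.30 − 1.96) = Φ(−0.31) = 38%
- d = 0.5, 27 progressors: Φ(0.5 × 4.39 − 1.96) = Φ(0.23) = 59%
- d = 0.8: 75% and 94%

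**Step 3: simulation, about 1,000 runs per setting.** The entries are false-positive rates. The first two contrasts are t-tests and the last two are Cox models.

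| d | Impaired who progress | Progressors vs healthy (not a planned test) | Progressors vs stable impaired | Cox, whole cohort, T1 status ignored | Cox, stratified by T1 status |
|---|---|---|---|---|---|
| 0.3 | 10% | 17% | 5% | 6% | 5% |
| 0.3 | 20% | 22% | 4% | 7% | 4% |
| 0.5 | 10% | 37% | 5% | 6% | 5% |
| 0.5 | 20% | 60% | 5% | 14% | 6% |
| 0.8 | 10% | 72% | 4% | 12% | 5% |
| 0.8 | 20% | 92% | 7% | 24% | 6% |
| 1.2 | 10% | 96% | 4% | 19% | 5% |
| 1.2 | 20% | 100% | 6% | 45% | 5% |

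**Step 4: a second set of assumptions.** With 67 per group and 1% of CHI, 3% of SCI and 15% of Group 3 progressing, the rates at d = 0.5 and 0.8 are about 27% and 55% against CHI. They are 11% and 21% in an unstratified cohort-wide dementia analysis, and about 5% when stratified.

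**Step 5: the regression on cognitive decline.** Here stable SCI and MCI participants count as non-decliners and CHI participants can have the event. With 67 per group, SCI shifted by d/4, and decline in 10-25% of CHI, 15-20% of SCI and 15% of Group 3 (all assumed), rejection is 4-7% for d = 0.3 to 0.8. With 30% of CHI and 25% of SCI declining it reaches 10% at d = 0.8, almost always in the opposite direction.

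**The case against.** The strongest reply has four parts.

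1. **No planned model compares progressors with CHI.** This stands. Stable SCI and MCI participants are in the regression and in the Cox risk set, and the main regression is close to its nominal error rate (step 5). A reader might infer from the main question that the whole analysis shares the fault, or that any marker of impairment will pass as a predictor. The documents do not support either. The large rates in the column against healthy people describe a contrast that the Statistical analyses section does not plan. Even in that contrast a weak marker is usually not significant (17-22% at d = 0.3).
2. **Stratification and risk sets are commonly left to an analysis plan, and the confounder list is open.** This stands in part: T1 status could still be added. But the comparator in the main question is stated, not left open, and an analysis plan written to answer that question would inherit it.
3. **Healthy participants may be meant as a normal-ageing reference.** That is a sensible role, and the tool is meant for older adults generally, so CHI belong in the cohort. It does not make them the comparator for a transition that they cannot undergo.
4. **The Cox exposure is decline in a marker, whereas the simulation uses a fixed shift in level.** This is a fair limit on the figures. The mechanism is the same if the rate of marker decline differs by T1 group, with d read as that difference, but the sizes are illustrative.

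**Conclusion.** The point holds in a limited form. The comparator in the main question is wrong for a question about transition. In the planned analyses the weakness is confined to the dementia Cox model as described, where omitting T1 status raises the false-positive rate for a pure impairment marker from about 5% to roughly 6-14% at d = 0.5 and 12-24% at d = 0.8. At d = 1.2 it can reach 45%. These sizes rest on assumed conversion rates, group shares and marker differences. The direction requires only that both the marker and the risk of dementia differ by T1 status. The change is worth making, but the point does not invalidate the design or the regression on cognitive decline.

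**What to change.** - Reword the main question so that the comparator is participants with the same cognitive status at T1 who do not progress.
- Stratify the dementia Cox model by T1 status (CHI, SCI, pMCI/MCI). For the transition question, add a version restricted to SCI and pMCI/MCI.
- Keep CHI as the normal-ageing reference and for the declines from CHI to SCI, pMCI or MCI. Do not name predictors of transition from the contrast with CHI alone.

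No new data are needed, since T1 status is already recorded for everyone. The cost is that apparent effects become smaller and the transition estimate rests on fewer participants (133 instead of 200 under the one-third-healthy assumption), with correspondingly wider intervals.
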